**Fig. 1 Fig1:**
[figure not shown]
The PBF Nutrition Scheme. ‘PBF Nut’ means ‘Under PBF Nutrition programme besides the existing PBF scheme’ while ‘Comp Nut’ means input based financing compensation besides the existing PBF scheme

The intervention at nutritional HC and hospital levels started in January 2015, involving 45 nutritional HCs and 29 district hospitals with the extended PBF scheme, as well as 45 nutritional HCs with the compensation scheme (control group). The interventions in the other type of HCs as well as at the CHW level were expected to start in summer 2015, but due to major political instability since April 2015, they have started respectively only in January 2016 and in October 2015.

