**Fig. 2 Fig2:**
[figure not shown]
Results chain of the introduction of nutrition criteria in the PBF grid

There is also a specific theory of change for the control HCs. The main design difference between the intervention and control groups is the formula to obtain the extra funding: each HC of the intervention group has to improve its own performance to increase its revenue; control HCs do not have any effort to do: they just have to hope that the intervention group, as a whole, will be performing. This choice for the definition of the two groups to compare indicates that the main causal path under investigation is the incentive one. Other tracks are not denied (see the qualitative part of the research) but are considered as secondary Table 2.

**Table 2 Tab2:** Routes applying in the Intervention and Control groups at the facility level

	Intervention group	Control group
(1) Income	++	++ ^a^
(2) Cash	++	++ ^a^
(3) Incentive	++ on nutrition services ? on other services	~
(4) Information	++	+ ^b^
(5) Supervision & enforcement	++	? ^c^
(6) Culture at provider level	~ or +	~ or + ^d^
(7) Health system	++	? ^e^

Notes: Symbols + and ++ mean that routes apply moderately to strongly; ? means unclear, ~ means neutral ^a^The control HCs will get additional financial resources which will correspond to a weighted average of the nutrition subsidies received in the intervention group. ^b^Before the start of the intervention, all 90 HCs were provided with some information on the nutrition indicators and on their performance in nutrition services. ^c^In a district where there are control and intervention HCs, the district team supervisors may transfer good practices to both intervention and control HCs. ^d^Control HCs know that there will probably be a scale up of the nutrition indicators to all HCs after the pilot; some managers may anticipate this by already reorganizing their nutrition services. ^e^Some health system effects might affect control HCs (e.g. if there is a problem of availability of nutritional inputs at national level, because of the pressure by intervention HCs, the supply to control HCs may be reduced)

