#### Sample size and randomization

The sample size of the household surveys is computed on the smallest difference in the main outcome that can be considered of public health significance, i.e. a reduction of about 25 % in acute malnutrition prevalence in intervention centres as compared to control centres. Assuming that the intervention will result in decreasing the prevalence of MAM in children aged 6–23 months from 10 % to 7.5 % [3], and assuming that 65 children aged 6–23 months are to be surveyed in the catchment area of each HC, 90 HCs were needed to be randomized to either the intervention or control group, for an α-error of 5 % and a β-error of 20 %. The number of children per HC was increased to 72 to allow for missing or incomplete data, amounting to a total of 6,480 children aged 6–23 months over the 90 selected HCs. In total, a sample of 6,480 children were surveyed for the baseline, and, two years after the start of the program, another sample of 6,480 children aged 6–23 months will be surveyed.

Selection of HCs invited to participate in the study was done by simple randomization (computer-based random selection) among the 193 eligible HCs, i.e. HCs providing nutrition services (treatment of SAM and MAM). The 90 selected HCs have been paired on essential parameters of organization and functioning in relation to the outcomes (MAM rehabilitation activity, volume of activity, population in the catchment area, and percentage of recovery among malnourished children) as measured during the baseline survey. This will then be used to control for the potential confounding effect of these parameters. Within each of the 45 pairs, allocation to the intervention was done randomly through a lottery system organized by the MoH during a workshop in December 2014.

Simple randomization should be applied to select the households to be surveyed in the catchment area of the 90 HCs. However, such an approach was difficult logistically and could have turned out to be extremely resource-consuming. The chosen alternative option was to sample clusters of households, i.e. households living close to each other. Six clusters of 12 eligible households were selected at random from the whole catchment area of a given HC. This could be done without expanding the overall sample size given the quite high intra-class correlation considered for the sample computation.

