## Discussion

This protocol relates to the measurement and understanding of the impact of an extension of the PBF program in Burundi to nutrition indicators.

This is an ambitious research project, by the multifactorial nature of the health problem addressed, the complexity of the intervention, the number of facilities participating and the set of international and national partners involved in the intervention and the evaluation. Moreover, there is today limited knowledge on how a PBF system addressing malnutrition should function, and the impact of the intervention is not guaranteed. By the date of submitting this paper (May 2016), we can report that this evaluation has to deal with three other unexpected challenges.

The first one relates to the incomplete clinic patient files and registers that could affect the power of ex-post calculation of the impact assessment at the HC level. To address this, we must advocate for good filling in and archiving of these files and registers.

A second limitation concerns the very low qualification of personnel. The critical issue here would be to enable (if possible) the HWs to attend training personalized to their needs, or at least to the needs identified for the HC as a whole. HCs managers formally expressed their demand for training and their willingness to pay for them, according to a Vickrey process: we plan to organise training for the HCs who showed most interest.

A third and final concern is obviously the political situation since April 2015 which has inevitably consequences on the health system. Indeed, some donors have already announced the cancellation of their budget support. We should also pay attention to donor decisions on the supply of inputs for the MAM.

This will be the first assessment of the extension of an existing PBF scheme to another set of indicators. The mixed methods design rests on the awareness that understanding the processes through which health interventions produce change is as important as measuring the actual change produced. It follows that a comprehensive assessment of health interventions can therefore only be achieved by coupling quantitative methods with qualitative ones as part of a systematic mixed methods study design [27].

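### Training organised by the evaluators is to go to the highest-bidding health centres, with no balance by arm or deferral past follow-up; depending on undated bids and training, it could confound the health-centre contrast

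*Protocol article*

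**What the plan says.** The Discussion of the protocol article dates its remarks: "By the date of submitting this paper (May 2016), we can report that this evaluation has to deal with three other unexpected challenges". The second of these is staffing: "A second limitation concerns the very low qualification of personnel". The response is training fitted to workers' needs, or at least to those of the centre. On who receives it, the article says "HCs managers formally expressed their demand for training and their willingness to pay for them, according to a Vickrey process", and then "we plan to organise training for the HCs who showed most interest". I read the bidders as the centres in the trial. No date is given for the bids or for the training.

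On timing, the Implementation section says "The intervention at nutritional HC and hospital levels started in January 2015". Sample size and randomization puts the lottery within the 45 pairs in December 2014 and the second household survey "two years after the start of the program".

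The Theory of change section describes the arm difference: "each HC of the intervention group has to improve its own performance to increase its revenue", whereas control centres receive an averaged sum that requires no effort from them. Demand for training is listed in General objectives and research questions as a possible spill-over. The quantitative Analysis strategy plan counts staff knowledge among the determinants of recovery and intends to adjust for it.

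**The concern.** The design takes care to equalise other inputs at the level of the health centre. Control centres get compensation matched on average, and all 90 centres were given some information before the start. Training has no such safeguard. It would go to a subset of randomised clusters, chosen by how much the manager bids.

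If the allocated arm influences the bid, the arms can end up with different shares of trained centres. Recovery rate and treatment duration are the main outcomes at health-centre level, and staff competence is a stated determinant of recovery. A difference between arms could then come partly from the incentive and partly from training that the evaluators supplied. The scheme described in the article does not include that training, and the article names the incentive as the main causal path under study.

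**Working it through.** **1. Timing.** The intervention started in January 2015. Two years later is about January 2017. The training plan is dated May 2016, about 16 months after the start and about 8 months before follow-up. Recovery is read from files of children registered in the six months before the facility survey. If that survey coincides with the household survey, the window opens about July 2016. Training in the second half of 2016 would therefore fall inside the period being measured. Delivery before follow-up is an inference from these dates and is not stated.

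**2. Can uptake differ by arm?** This depends on when the bids were made.
- Before the December 2014 lottery: the bid is a pre-randomisation characteristic. The expected difference in trained share is zero, and only chance imbalance remains.
- After the lottery: only intervention centres must perform to earn more, so training may be worth more to their managers. The article itself lists training demand as a possible spill-over.

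**3. The plan's own figure.** Recovery 80% vs 90%, α 5% (two-sided assumed), power 80%, ICC 0.15, 45 centres per arm.
- Individually randomised: 199 files per arm (no continuity correction).
- With m files per centre: 45m = 199 × [1 + 0.15(m − 1)], which gives m = 11.17, rounded up to 12. The stated 12 files per service is reproduced.
- At m = 12 the design effect is 1 + 11 × 0.15 = 2.65, the effective size is 45 × 12 / 2.65 = 203.8 per arm, and power is 81%.
- Standard error of the difference at 80% recovery in both arms: √(2 × 0.8 × 0.2 / 203.8) = 3.96 points (pairing ignored).

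**4. Bias.** Bias = training effect × (trained in intervention − trained in control) / 45. The article gives neither the numbers trained nor the training effect, so both are assumed. The last column is the chance of a significant result when the scheme itself has no effect.

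| Trained, intervention vs control | Training effect (points) | Bias (points) | False-positive rate |
|---|---|---|---|
| 5 vs 5 | any | 0 | 5.0% |
| 10 vs 5 | 5 | 5 × 5/45 = 0.6 | 5.2% |
| 20 vs 5 | 5 | 5 × 15/45 = 1.7 | 7.0% |
| 30 vs 10 | 5 | 5 × 20/45 = 2.2 | 8.7% |
| 10 vs 5 | 10 | 10 × 5/45 = 1.1 | 5.9% |
| 20 vs 5 | 10 | 10 × 15/45 = 3.3 | 13.4% |
| 30 vs 10 | 10 | 10 × 20/45 = 4.4 | 20.2% |

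**5. Reverse imbalance.** If more control centres were trained and control recovery rose by 1, 2 or 3 points, power to detect a true rise to 90% would fall from 81% to 73%, 64% or 54%.

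**The case against.** The strongest counter-argument is that much of this is not in the text. Each part of it is taken in turn.

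- **Dates.** A reader might infer that training will certainly be delivered during the trial. The article gives no training date, and the figure showing the study stages is not available. The May 2016 date makes earlier delivery plausible and no more. This stands.
- **Direction.** A reader might infer that intervention centres bid more. The bids are undated and may precede the lottery. Even if they came later, control centres hold comparable funds, and the notes to Table 2 allow that some of their managers anticipate scale-up. Either sign is possible. This stands.
- **Content.** The training is not said to concern nutrition, and staff knowledge is not itself a main outcome in Table 3. The link to recovery and treatment duration is reasonable, because the article treats staff knowledge as a determinant of recovery. The link to community prevalence is less direct.
- **Causal path.** Demand for training, and willingness to pay for it, may be partly a genuine effect of the scheme, so not all of a difference would be bias. This stands for demand. The supply is organised by the evaluators and lies outside the scheme as described.
- **Set aside elsewhere.** The article says that training demand is not covered in this paper. That sets aside the assessment of demand. It does not deal with what delivering training does to the main contrast.
- **Adjustment.** If the bids preceded allocation, they are a baseline covariate and could be used, so it would be too strong to say that no adjustment could help. The adjustment actually planned is for staff knowledge. Measured after training, that is a post-randomisation variable: adjusting for it may leave confounding by managers' motivation and remove part of the scheme's own effect.

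**Conclusion.** The point holds as a conditional weakness of the stated plan. The article commits to evaluator-organised training for the highest bidders among the randomised centres, and it neither balances this by arm or pair nor defers it. Two facts decide whether harm follows, and neither is given: whether training precedes the follow-up survey, and whether the bids followed the lottery. If both are so, the contrast in recovery and treatment duration may combine the incentive with training from outside the scheme.

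Under the assumed inputs the bias in recovery lies between 0 and 4.4 points, up to 44% of the 10-point target, and it could have either sign. No single value in that range is supported by the document. If the bids came first, the expected bias is zero. The article does not support the stronger claim that the trial result is already biased, or biased in favour of the scheme.

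**What to change.** Deliver the training after the follow-up household and facility surveys are complete in all 90 centres. This removes the problem whatever the bid dates were.

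If it cannot wait, allot the training slots equally by arm: the same number of top bidders in each arm, or both centres of a pair whenever either is selected. The difference in trained share is then zero, and so is the bias in the formula above, provided training works equally well in both arms.

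In either case, record the bid date, training dates and attendance, and report them by arm. Do not rely on adjustment for staff knowledge measured after training. A contrast restricted to untrained pairs can be shown as supportive only, because those pairs are themselves selected by the bids.

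The cost is a delay of some months, so the remedy for low staff qualification arrives later, plus a small log of dates and attendance. The pair option also means training some centres that would not have been selected on their own bid.

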## Abbreviations

CHW, Community Health Workers; FGDs, Focus Group Discussions; GDP, Gross Domestic Product; HAZ, Height-for-Age Z-score; HC, Health Centre; HIV/AIDS, Human immunodeficiency virus infection/acquired immune deficiency syndrome; ICC, inter-cluster correlation; IDI, in-depth interview; ITM, Institute of Tropical Medicine of Antwerp, Belgium; LMICs, low- and middle-income countries; MAM, Moderate Acute Malnutrition; MDGs, Millenium Development Goals; MoH, Ministry of Health; MSPLS, Ministère de la Santé Publique et de la Lutte contre le SIDA; MUAC, Mid-Upper Arm Circumference; PBF, Performance Based Financing; SAM, Severe Acute Malnutrition; UNICEF, Fonds des Nations unies pour l’enfance; UZA, University of Antwerp; WB, World Bank; WFP, World Food Programme; WHZ, Weight-for-Height Z-score
